## Background and Rationale

3D printed models can aid and improve medical education. Tangible 3D models may help patients better understand their medical condition and surgical procedure. Studies that have analyzed patient education using 3D printed models span specialties from ENT, urology, cardiology, and general surgery. However, there is a lack of studies analyzing this relationship within the colorectal patient population. Most studies focus on preoperative education, but few look into the relationship between shared decision-making and patient anxiety. Surgical patients often report a poor understanding of their disease and treatment plan. Additionally, patients report low involvement in their healthcare, given the low application of shared decision-making principles. Thus, the focus of this study will be to evaluate the effect of preoperative medical education using 3D printed models on patient's perspective of shared decision-making and patient anxiety in the colorectal patient population. There is also a paucity of literature reviewing whether health literacy impacts patient education with 3D models. Thus, a secondary focus of this study will be to evaluate whether the patient's health literacy contributes to different outcomes in anxiety and shared decision-making.

## Specific Aims

The study aims to evaluate the benefit of 3D-printed models in preoperative patient education. We will recruit patients scheduled for colorectal surgery who present to the Vanderbilt University Medical Center Colorectal Clinic.

Aim 1: Investigate the effect of integrating a 3D model in patient-clinician interaction on patients' perception of shared decision-making. We will accomplish this by administering the validated Shared Decision-Making Questionnaire (SDM-Q-9) (Figure 1) among patients after their preoperative consultation and comparing the results of study cohorts (control vs. intervention arm).

Aim 2: Evaluating the change in anxiety and procedural-specific knowledge after incorporating a 3D model compared to standard care. To assess the change in anxiety, we will utilize the validated six-item State-Trait Anxiety Inventory questionnaire (STAI-6) (Figure 2). For evaluating a differential change in patient knowledge, we will use the Patient Education Assessment survey (Figure 3) and compare scores for two scales between the study cohorts.

Aim 3: Investigating the effect of health literacy on the outcomes of Aim 1 and Aim 2. We will categorize patients based on health literacy as described by the BRIEF: Health Literacy Screening Tool (Figure 4) and compare SDM-Q-9 score and the change in STAI-6 and Patient Education Assessment scores between the study cohorts.

Primary hypothesis: Patients educated preoperatively using 3D-printed models will perceive increased levels of shared decision-making, suffer lower procedural anxiety, and have an improved understanding of the procedure compared to standard care (using 2D images for patient education).

Secondary hypothesis: The primary hypothesis will be consistent across health literacy categories.

## Trial Design

We will conduct a single-center pilot cluster randomized control superiority trial. Participating surgeons will be randomly assigned to either the control arm (standard care) or the intervention arm (3D-printed model) using the opaque sealed envelope method. Patients will be recruited in a cluster and study cohort, depending on the next available surgeon. A 1:1 enrollment ratio will be targeted (Figure 5). Blinding will not be performed.

## Inclusion/Exclusion Criteria

Patients will be recruited from the colorectal surgery clinics of Vanderbilt University Medical Center, a tertiary care hospital in Nashville, TN, USA. Our inclusion and exclusion criteria are as follows:

| INCLUSION                                                              | EXCLUSION                       |
|------------------------------------------------------------------------|---------------------------------|
| Age over 18 years                                                      | Non-English speaker             |
| Scheduled for partial or complete resection of the colon and/or rectum | Unable to give informed consent |

## Patient Participation / Enrollment

Six consenting colorectal surgeons will be randomly assigned to study arms (standard care vs. intervention) using the opaque sealed envelope method by the research nurse. All consenting patients who meet the inclusion criteria will be assigned to the next available surgeon by personnel unrelated to this study. Patients will then be asked to complete preoperative questionnaires (as per protocol) to measure baseline anxiety levels (STAI-6) and current medical knowledge (Patient Education Assessment). Following, one group will receive traditional education from their physician using 2D images, whereas the other patient cohort will receive the same education but with a 3D printed model (Figure 6). Subsequently, both groups will take the SDM-Q-9 questionnaire and retake the STAI-6 and Patient Education Assessment surveys (Figure 5). **There will be no subject randomization in this study.** Participant enrolment, assignment to study arms, and cluster randomization will be performed by persons unrelated to the research. The cluster randomization method will be used to prevent the mixing and contamination of the intervention. This study will be conducted per the current version of the Declaration of Helsinki and in agreement with the International Conference on Harmonization guidelines on Good Clinical Practice.

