## Study Procedures and Data Collection

Recruitment: Surgical patients presenting to the colorectal clinic of a tertiary care hospital will be recruited during their preoperative visit.

Informed Consent: Patients who agree to participate in the study will be assessed to confirm eligibility and given a consent form from a clinic nurse or study investigator. All study-related questions will be answered before they agree to sign the written informed consent document, which will be recorded in the Research Electronic Data Capture (REDCap) database.

Study Visit: Surgical patients will be asked to complete the study questionnaires before their preoperative consultation (STAI-6 and Patient Education Assessment) before their consultation and SDM-Q-9, STAI-6, and Patient Education Assessment after the consultation at their preoperative consultation. These patients will only participate in the study during this visit and will not require any follow-up.

SDM-Q-9: This is a validated, nine-item self-report survey that measures how involved patients feel in the decision-making process with their healthcare provider . This survey will only be administered once, post-consultation (Figure 1).

STAI-6: This validated six-item tool  will be used to measure the patient's anxiety levels before and after the preoperative consultation to establish a baseline and understand how each intervention affects anxiety levels (Figure 2).

Patient Education Assessment: The 13-question survey aims to assess patients' knowledge and understanding of their colon anatomy, disease, procedure, and complication risks. This survey will be given both before and after informed consent to assess any changes (Figure 3).

The baseline demographic and clinical information of each patient will be collected by the research nurse at the preoperative visit, recorded in the institutional REDCap database, and compared between the study arms.

REDCap Data Entry: This project will utilize the REDCap electronic data capture tools hosted at Vanderbilt University Medical Center for data collection and management. REDCap will be used to capture all recruited patients who are enrolled in the study and store their individual data as well as study consent documentation.

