## Statistical Considerations

Sample size: Since we do not have prior data in this patient cohort to appropriately power or simulate our analysis, we used the mean and standard deviation of SDM-Q-9 in the literature [86.7 ( $\pm 11.6$ )]. To ensure that this study has adequate power to detect a clinically meaningful effect size and provide data for future studies, we assume a 5% risk of type I error and a 20% risk of type II error, a 1:1 enrollment ratio, and a targeted increase of 3 times the minimal clinically important difference ( $4^{17}$ ). This means that 20 patients needed to be allocated to each arm. Since this intervention has not been utilized in colorectal patients before, we target an expected rejection rate of 50%, meaning 80 patients should be approached (40 in each arm).

Data analysis plan: Patient characteristics will be compared between the 3D-printed model and standard care arms with the chi-squared test for categorical variables and the Student's t-test for comparisons between continuous variables. The postintervention SDM-Q-9, the preintervention and postintervention STAI-6, and the Patient Education Assessment Questionnaire scores will be compared between the study arms using the restricted maximum-likelihood estimation to account for the intraclass differences. The postintervention score will be treated as a dependent variable, while the preintervention score will be treated as a covariate. A similar subgroup analysis will be conducted after dichotomizing health literacy into adequate (17-20) and inadequate or marginal ( $<17$ ) groups. The level of significance will be at  $\alpha = 0.05$  throughout the manuscript. Statistical analyses will be performed using Stata (version 17, StataCorp LLC, College Station, TX). We do not plan on conducting any interim analysis.

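### The stated safeguard, that people outside the research enrol and allocate, is contradicted within the protocol, and nothing keeps recruitment or baseline reporting unaware of the arm

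*Protocol*

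**What the plan says.** On who does what, the protocol's section Patient Participation / Enrollment states: "Participant enrolment, assignment to study arms, and cluster randomization will be performed by persons unrelated to the research". Earlier in that section the six surgeons are randomised "using the opaque sealed envelope method by the research nurse". Under Study Procedures and Data Collection, patients who agree to take part are "given a consent form from a clinic nurse or study investigator".

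On order, Patient Participation / Enrollment says: "All consenting patients who meet the inclusion criteria will be assigned to the next available surgeon by personnel unrelated to this study". It then lists the baseline STAI-6 and knowledge survey, the consultation, and the post-consultation forms. Trial Design puts it this way: "Patients will be recruited in a cluster and study cohort, depending on the next available surgeon". The description of the Patient Education Assessment in Study Procedures and Data Collection says: "This survey will be given both before and after informed consent to assess any changes".

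Trial Design also states that there is no blinding, and Patient Participation / Enrollment that patients are not individually randomised.

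**The concern.** Once a surgeon's envelope is opened, that surgeon's arm is fixed and open for the whole trial. Anyone who knows which surgeon a patient will see knows the arm. In a cluster trial of this kind, protection against selection comes from who recruits, what they know, and whether consent and baseline measurements are complete before the arm can be known. The protocol relies on the first of these and contradicts itself on it. It is silent on the second and not uniform on the third.

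Two things are at stake. First, patients who consent could differ between arms, and the planning assumption that half of those approached will refuse leaves room for this. The mixed model estimated by REML accounts for clustering by surgeon, not for selection. SDM-Q-9, one of the two primary outcomes, is measured only after the consultation, so no baseline score can reveal or adjust for a difference. Second, baseline anxiety and knowledge scores enter the model as covariates. If patients answer them knowing, or guessing, their arm, the adjustment itself can carry a difference between arms.

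**Working it through.** **Who performs each step.** The general statement covers three steps. Set against the rest of the text:

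- *Randomising surgeons.* The general statement gives this to people outside the research, but the same section gives it to the research nurse. That nurse has a study task: demographic and "clinical information of each patient will be collected by the research nurse at the preoperative visit". The two statements conflict.
- *Enrolling patients.* The general statement gives this to outsiders as well, but a study investigator may hand over the consent form. An investigator is part of the research, so these conflict too.
- *Assigning patients to surgeons.* This is given to personnel outside the study in both places, so it is consistent.

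Two of the three steps are contradicted and one is not.

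**In what order.**

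- Patient Participation / Enrollment: consent, then surgeon (and so arm), then baseline forms, then consultation, then post-consultation forms.
- Trial Design: recruitment into a cluster and cohort that depends on the surgeon. This may be shorthand for the sequence above, or may mean that the surgeon is known at recruitment.
- Inclusion/Exclusion Criteria and the recruitment paragraph: patients already have a resection scheduled and are recruited at the preoperative visit. A surgeon may therefore already be booked; the protocol does not say.
- Knowledge survey: the Study Visit paragraph and Patient Participation / Enrollment time it around the consultation. The survey's own description times it around informed consent.

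**Where the arm could become known too early.** If Patient Participation / Enrollment is followed to the letter, consent precedes assignment and is protected, but the baseline forms follow an open assignment and are not. If the surgeon is known at recruitment, neither is protected. No section says that the person approaching or consenting patients is kept unaware of the surgeons' allocation.

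**The plan's own figure.** 20 per arm with 50% refusal gives 20 / (1 − 0.5) = 40 per arm, and 2 × 40 = 80 approached. This reproduces the stated number.

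**Illustration of size (assumptions not in the documents).** Suppose that in one arm only, the 50% who consent are the upper half on a normally distributed trait that correlates r with SDM-Q-9, and that the other arm has no selection. The mean of the upper half of a standard normal is 0.798. With the protocol's SD of 11.6:

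shift = r × 0.798 × 11.6

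- r = 0.2: 0.2 × 0.798 × 11.6 = 1.85 points, which is 1.85 / 12 = 15% of the target difference (3 × 4 = 12).
- r = 0.4: 0.4 × 0.798 × 11.6 = 3.70 points, which is 3.70 / 12 = 31% of the target and just under the cited minimal important difference of 4.

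With 20 per arm and clustering ignored, a two-sided 5% test with no true effect would then reject in about 8.0% and 17.9% of trials. No comparable figure can be given for STAI-6, because the protocol states no SD for it.

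**The case against.** The best defence is that the protocol does give one workable sequence. Patient Participation / Enrollment puts consent before assignment and leaves assignment to personnel outside the study. The Study Visit paragraph agrees on the timing of the forms around the consultation, and Trial Design can be read as a summary of the same rule. That is fair, and it limits the point: consent is protected if that section is followed. The conflict over who enrols remains, as does the placement of baseline forms after open assignment.

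Four stronger readings are tempting, and the document does not support them.

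- A reader might infer from "meaning 80 patients should be approached (40 in each arm") that the arm must be known before consent. It need not be: 20 / 0.5 is ordinary planning arithmetic under a 1:1 target and says nothing about when the arm is known.
- A reader might infer from the informed-consent wording that knowledge data are collected before study consent, or that both surveys precede the education. Patient Participation / Enrollment gives the baseline survey to consenting patients and the repeat after the education. The phrase may mean surgical consent at the consultation. It is a conflict or an ambiguity in wording, not evidence of either practice.
- A reader might infer that the nurse's handling of the envelopes biases patient selection. Opening envelopes for six surgeons once does not of itself affect who consents later. That conflict weakens the stated safeguard; the conflict over who takes consent is the one that bears on recruitment.
- A reader might take the illustrated shifts as an estimate. Nothing in the document supports those correlations or selection in one arm only, and the trial is aimed at 12 points. Baseline characteristics will also be compared between arms, so gross selection need not go unseen.

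It is also fair to say that keeping clinic staff unaware of which surgeons use a physical model may prove impracticable at a single center. The study schema (Figure 5) is not visible in the text at hand, so it cannot be used to settle the order either way.

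**Conclusion.** The point stands in a limited form. The contradiction over who randomises and who enrols is explicit and rests on no assumption. That differential consent or baseline reporting is possible follows from open, fixed surgeon allocation together with the absence of any rule keeping the recruiter unaware of it; the protocol does not show that it will happen. How far consent is exposed depends on which section is followed. The exposure of the baseline STAI-6 and knowledge survey exists even under the most protective reading. The magnitude is unknown: the 1.85 and 3.70 points show what modest selection could do to SDM-Q-9, not what to expect. The timing phrase for the knowledge survey needs correction whichever consent was meant. This should be corrected because the remedy is cheap and a bias introduced at recruitment cannot be removed by the planned model.

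**What to change.** 1. State one sequence in Trial Design, Patient Participation / Enrollment, and Study Procedures and Data Collection: eligibility; study consent; baseline STAI-6 and knowledge survey; surgeon assignment by clinic scheduling staff (or, if the surgeon is already booked, disclosure of the arm); consultation; post-consultation forms. This changes the order now in Patient Participation / Enrollment, which assigns the surgeon before the baseline forms.
2. Remove the study-investigator option for giving out the consent form. Clinic staff should take consent, where feasible without knowing the surgeons' allocation.
3. Name one non-study role to open the envelopes, and remove the research nurse from that step.
4. In the Patient Education Assessment paragraph, time the survey before and after the consultation instead of informed consent.
5. Record the numbers approached and refusing by surgeon, so that differential consent can be seen.

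The cost is protocol wording and a small change to the clinic-day workflow with existing staff. If recruiters cannot be kept unaware of the allocation, the protocol should list recruitment bias under Limitations of Study. No change to the sample size follows from this.

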## Outcome Measurements

**Primary Outcome Measures:** The difference in the levels of shared decision-making using the validated SDM-Q-9 questionnaire (Figure 1) and the differential change in anxiety levels post-intervention using the validated STAI-6 questionnaire (Figure 2).

**Secondary Outcome Measures:** A differential change in the patient knowledge level captured by our 13-question Patient Education Assessment survey (Figure 3) and evaluating if the change is consistent when categorized by health literacy scores based on the BRIEF: Health Literacy Screening Tool (Figure 4).

## Study Procedures and Data Collection

Recruitment: Surgical patients presenting to the colorectal clinic of a tertiary care hospital will be recruited during their preoperative visit.

Informed Consent: Patients who agree to participate in the study will be assessed to confirm eligibility and given a consent form from a clinic nurse or study investigator. All study-related questions will be answered before they agree to sign the written informed consent document, which will be recorded in the Research Electronic Data Capture (REDCap) database.

Study Visit: Surgical patients will be asked to complete the study questionnaires before their preoperative consultation (STAI-6 and Patient Education Assessment) before their consultation and SDM-Q-9, STAI-6, and Patient Education Assessment after the consultation at their preoperative consultation. These patients will only participate in the study during this visit and will not require any follow-up.

SDM-Q-9: This is a validated, nine-item self-report survey that measures how involved patients feel in the decision-making process with their healthcare provider . This survey will only be administered once, post-consultation (Figure 1).

STAI-6: This validated six-item tool  will be used to measure the patient's anxiety levels before and after the preoperative consultation to establish a baseline and understand how each intervention affects anxiety levels (Figure 2).

Patient Education Assessment: The 13-question survey aims to assess patients' knowledge and understanding of their colon anatomy, disease, procedure, and complication risks. This survey will be given both before and after informed consent to assess any changes (Figure 3).

The baseline demographic and clinical information of each patient will be collected by the research nurse at the preoperative visit, recorded in the institutional REDCap database, and compared between the study arms.

REDCap Data Entry: This project will utilize the REDCap electronic data capture tools hosted at Vanderbilt University Medical Center for data collection and management. REDCap will be used to capture all recruited patients who are enrolled in the study and store their individual data as well as study consent documentation.

## Adverse Events or Unanticipated Problems

Given that this survey will be offered during the patients' normal preoperative clinic visit, we do not expect any adverse events or unanticipated problems. However, if an adverse event occurs, the principal investigator will report events according to IRB policies and procedures.

## Risks of Study Procedures and Data Confidentiality

Since this study will only utilize a computerized assessment during the patient's preoperative visit, we anticipate no associated risks to participating, except for loss of confidentiality.

Data monitoring committee: A data monitoring committee will not be involved since we do not anticipate any adverse events, and this trial does not involve vulnerable populations. However, the study PI will perform weekly audits on trial conduct, data collection and adherence to protocol.

Data confidentiality: All recorded clinical data identifying the subject will be collected and secured using the REDCap electronic data capture tools hosted at Vanderbilt University Medical Center,

which only study investigators can access. Patient privacy and confidentiality will be prioritized throughout the study and ensured by assigning an individualized number to each study participant as the identifier instead of their name. Only the principal investigator and co-investigators will have the list of study patient's names. All data will be maintained in a HIPAA-compliant, password-protected institutional database. Project team members listed as Key Study Personnel with existing Epic access rights may also be granted the use of REDCap Dynamic Data Pull (DDP) tools. These tools are designed to enable the transfer of relevant study-related data from the Vanderbilt Research Derivative into REDCap.

